## Abstract

With therapeutic trials on the horizon for Charcot-Marie-Tooth type 1A (CMT1A), reliable, valid, and responsive clinical outcome assessments and biomarkers are essential. Accelerate Clinical Trials in CMT (ACT-CMT) is an international study designed to address important gaps in CMT1A clinical trial readiness including the lack of a validated, responsive functional outcome measure for adults, and a lack of validated biomarkers for multicenter application in clinical trials in CMT1A. The primary aims of ACT-CMT include validation of the Charcot-Marie-Tooth Functional Outcome Measure, magnetic resonance imaging of intramuscular fat accumulation as a lower limb motor biomarker, and *in-vivo* reflectance confocal microscopy of Meissner corpuscle sensory receptor density, a sensory biomarker. Initial studies have indicated that these measures are feasible, reliable and valid. A large prospective, multi-site study is necessary to fully validate and examine the responsiveness of these outcome measures in relation to existing outcomes for use in future clinical trials involving individuals with CMT1A. Two hundred 15 adults with CMT1A are being recruited to participate in this prospective, international, multi-center study. Serial assessments, up to 3 years, are performed and include the CMT-FOM, CMT Exam Score-Rasch, Overall Neuropathy Limitations Scale, CMT-Health Index, as well as nerve conduction studies, and magnetic resonance imaging and Meissner corpuscle biomarkers. Correlations using baseline data will be examined for validity. Longitudinal analyses will document the changes in function, intramuscular fat accumulation, Meissner corpuscle sensory receptor density. Lastly, we will use anchor-based and other statistical methods to determine the minimally clinically important change for these clinical outcome assessments and biomarkers in CMT1A. Reliable, and responsive clinical outcome assessments of function and disease progression biomarkers are urgently needed for application in early and late phase clinical trials in CMT1A. The ACT-CMT study protocol will address this need through the prospective, longitudinal, multicenter examination in unprecedented detail of novel and existing clinical outcome assessments and motor and sensory biomarkers, and enhance international clinical trial infrastructure, training and preparedness for future therapeutic trials in CMT and related neuropathies.

## Introduction

Charcot-Marie-Tooth disease (CMT) is a family of rare inherited peripheral neuropathies affecting ~1:2,500 individuals. CMT1A accounts for 50% of all people with CMT and is caused by an intrachromosomal duplication in chromosome 17 that results in the overexpression of peripheral myelin protein 22 kDa (PMP22) (1, 2). CMT1A is characterized by progressive weakness, imbalance, sensory loss, foot drop, and gait abnormalities resulting in reduced health-related quality of life (HRQoL) (3, 4). In the absence of pharmacologic interventions, treatment mainly consists of symptom management rehabilitation and surgical strategies. Research efforts, most recently, focus on disease modifying treatments including targeting correcting PMP22 overexpression using antisense oligonucleotides, small interfering RNA or small molecules as candidate therapies (5). Other therapeutic targets that have demonstrated preclinical or early clinical promise include inhibition of P2X7 receptor overexpression (6), neurotrophin 3 administration via gene therapy (7), and PP1R15A inhibition (to prolong unfolded protein response and reduce cell stress) (8). Most recently, a trial of a myostatin inhibitor did not demonstrate efficacy in regards to functional improvements (9).

Previously, ascorbic acid was thoroughly evaluated in individuals with CMT1A, with no benefit detected in multiple clinical trials (10–12). The primary outcome measure for the trials of ascorbic acid, the CMT Neuropathy Total Score (CMNTS), did not show significant change over a 2 year period in adults. These studies highlighted the need for additional natural history data as well as the development of reliable, responsive and clinically meaningful outcome assessments (COAs) in order for the CMT community to demonstrate clinical trial readiness (13). The Inherited Neuropathy Consortium (INC) has since done much work developing outcome measures and collecting natural history on the many different sub-types of CMT. As part of this work, the CMTNS was revised as a measure of disease severity to the CMTNS Version 2 (CMTNSv2) and then underwent Rasch analysis (CMTNSv2-R) (14, 15). Functional scales including the CMT Pediatric Scale (CMTPedS) and CMT Infant Scale (CMTInfS), have been developed and validated (16, 17). Using data from the INC, the CMTPedS detected disease progression in children with CMT1A over a 2 year period (18). Lastly, patient reported outcomes (PROs) to elucidate the individual's perspective of their disease have been developed and validated (19). Despite these achievements, there are still gaps in COAs for measuring the impact that CMT has on function. To address this limitation, we have developed and piloted the CMT-FOM (CMT-FOM), a measure for adults with CMT, modeled on the validated CMTPedS (20, 21). The CMT-FOM assesses physical function, including hand function, leg function/mobility and balance, areas that have been identified as having an impact on quality of life in individuals with CMT (22). This measure, once validated, will fulfill a critical need for future clinical trials in CMT as well as address a key element identified by the FDA for regulatory approval.

Beyond the need for COAs that are responsive to change, there is also a need for complementary biomarkers including target engagement measures and measures of treatment response that can be used in early phase clinical trials. Specifically, magnetic resonance imaging (MRI) to measure intramuscular fat accumulations (IMFA) in the calf (Figure 1) (23, 24) has, in pilot studies, detected disease progression in CMT1A over 12 months, the most responsive assessment to date in this disorder. Sensory dysfunction contributes significantly to functional impairment and reduced quality of life in CMT1A, yet objective measures of sensory dysfunction are lacking in CMT1A, with sensory nerve action potentials often unelicitable. *In vivo* reflectance confocal microscopy is non-invasive, and painless and has detected reductions of Meissner corpuscle density (RCM of MC density) in CMT1A that correlate with elevations of touch pressure sensory thresholds and clinical severity (25, 26). These motor and sensory biomarkers require longitudinal, multicenter validation prior to application in CMT1A clinical trials.

**Figure 1 F1:**
[figure not shown]
Example T1-weighted MRI images, and three-point Dixon MRI-obtained quantitative fat-fraction maps, from a healthy volunteer **(top images)**, and a person with CMT1A **(bottom images)**.

Therefore, the goal of the Accelerate Clinical Trials in CMT study (ACT-CMT) is to validate COAs and biomarkers for use in clinical trials involving adults with CMT1A. Specifically, we will evaluate the reliability, examine the construct and convergent validity, and document responsiveness to disease progression of the CMT-FOM. Similarly, using quantitative three-point Dixon MRI, we will examine the reliability, convergent validity and responsiveness to change of IMFA as measured by muscle fat fraction (FF) to validated it as a biomarker of calf-level muscle involvement, and last, we will assess the reliability, construct and convergent validity and ability to detect change of RCM of MC density to validate it as a sensory disease progression biomarker for use in multi-site CMT1A trials. We also aim to increase the efficiency of trial design by using data to refine eligibility criteria.

## Methods

### Study Description

The ACT-CMT study is a prospective, international, multi-center study of 215 individuals over a 3-year period. The University of Rochester, University of Iowa, and University of Pennsylvania are the enrolling sites in the United States and the European sites are University College London, UK and Fondazione IRCCS Istituto Neurologico Carlo Besta in Milan, Italy. The University of Rochester is the overall coordinating center for the study, providing training and quality assurance for all COAs, and is serving as the central training, quality assurance and reading core for blinded quantitation of MC densities from RCM image sets. The University College of London (UCL) MRC Neuromuscular Disease Centre is the central site for training, quality assurance and analysis of MRI of IMFA. The University of South Florida is the Data Management Center, and the University of Sydney will provide expertise in COA training and Rasch modeling for the CMT-FOM.

### Training and Quality Assurance

Principal investigators (PIs), study coordinators and clinical evaluators (CEs) attended an Investigators Meeting prior to the initiation of the study and participant enrollment. Study personnel received detailed procedure manuals for all assessments. Standardization and training in the administration and scoring of the CMTNSv2 was performed with the PIs and CEs. Following the meeting, the CEs participated in a hands-on training for administering the CMT-FOM. Following this training, evaluators assessed 10 individuals over 2 days to examine reliability (27). In addition to the training for the MRI assessments, the central MRI Reading Center (UCL) approved inter–scan reproducibility of control subjects at each site prior to beginning MRI assessments. MRIs are reviewed for image quality by the UCL MRI core with ongoing feedback to sites, and remedial steps as needed to rapidly address any data quality issue.

For RCM imaging, the University of Rochester RCM Core provided initial training for procurement of RCM image sets at the in-person meeting. Additional study personnel were trained by peers and remotely with real time feedback by RCM reading center staff using the microscope's TeamViewer application. Image sets are uploaded to the RCM Core and reviewed for image quality with ongoing feedback to sites (Figure 2).

**Figure 2 F2:**
[figure not shown]
Test-retest fat-fraction map images from an example healthy volunteer for the calculation of reproducibility metrics. Images were acquired at two time points, 2 weeks apart. The fat fraction map was calculated from three-point Dixon acquisitions using the MRI study protocol, and shown with the placement of the whole muscle ROIs overlaid on the slice. All images were windowed to the same range for display (0–100%).

### Recruitment of Participants

Subjects with CMT1A are primarily being recruited through the hereditary neuropathy and neuromuscular clinics led by the investigator at each site. Additionally, CMT1A subjects participating in the INC Rare Disease Clinical Research Network (RDCRN) studies at these sites are also given the opportunity to participate in the ACT-CMT study. An Institutional Review Board approved letter may also be sent to the participants of the INC RDCRN contact registry to inform them of the study and lastly, information about the study is posted on the websites of patient advocacy groups including CMT Association and the Hereditary Neuropathies Foundation. Control participants for this study are being recruited via postings in common areas at the sites that are accessible to a variety of individuals who travel through those areas. Control participants undergo MRI and RCM assessments only.

### Study Population

Individuals between the ages of 18 and 75 years with mild to moderate CMT1A will be recruited to participate in this study. This age range was selected as it is the age range that mirrors what is anticipated to be used in future adult CMT1A treatment trials.

In addition, all study participants are required to be ambulatory (assistive devices allowed) and have clinical and electrophysiological features of CMT1A, with a documented PMP22 gene duplication in the participant, or in an affected first degree relative, with documented nerve conduction slowing consistent with a diagnosis of CMT1A. The individuals are required to be able to participate in the informed consent process and document their consent. They must also be able to speak and read English (or Italian for the Italian site). Individuals are excluded from participation if they have other neuromuscular disorders, diabetes, exposure to peripheral neurotoxic agents, or other conditions known to predispose them to peripheral neuropathy. They are also excluded if foot or ankle surgery is planned or done within the 9 months preceding the screening, or have a medical condition that in the opinion of the investigator precludes participation in the CMT-FOM data collection. For the MRI study procedures, individuals are additionally excluded from participation if there is a contraindication for non-contrast MRI.

Healthy controls of the same age range participating in the MRI and/or RCM assessments are required to be able to provide written informed consent. They must also be able to speak and read English (or Italian for Italian site). Healthy control participants are required to meet the same exclusion criteria outlined above for participants with CMT1A. Additionally, individuals are excluded from participation if they have a family history of a known hereditary neuropathy, unless previously been shown to be negative for PMP22 gene duplication/deletion.

## Measures

To address the objectives of this study, participants complete assessments at baseline, and every 6 months for up to 36 months. Depending on the time of enrollment, participants will complete either a 30- or a 36-month end of study visit, but not both. Participants will be asked to complete the CMT-FOM, MRI and RCM assessments (Table 1). In addition, measures of disease severity and burden, sensory assessments, the fibular distal compound muscle action potential (CMAP) recording from the tibialis anterior muscle, and blood specimens will be collected. Participants will also complete a global impression of change questionnaire.

**Table 1 T1:** Schedule of activities.

**Study visit**		**Screen**	**1**	**2**	**3**	**4**	**5**	**6**
Timeframe (months)		0	0	6	12	24	30	36
Activities for all participants	Informed Consent	x						
	Demographics	x						
	Medical history	x		x	x	x	x	x
	Concomitant medications	x		x	x	x	x	x
	CMTES	x	x	x	x	x	x	x
	CMTNSv2-R (CMTES + tadial SNAP and ulnar CMAP)*		x		x	x		x
	Peroneal [tibialis anterior (TA)] CMAP amplitude		x		x	x		x
	CMT-FOM (up to 10 subjects will also perform CMT-FOM reliability testing)		x	x	x	x	x	x
	PROs: CMTHI, ONLS, PGIC		x	x	x	x	x	x
	Adverse Events	x	x	x	x	x	x	x
	Blood draw for Biomarkers		x	x	x	x	x	x
Additional AIM 2 items	MRI thigh and calf muscle IMFA		x		x	x		
Additional AIM 3 items	RCM MC density digit V and thenar eminence		x	x	x	x	x	x
	Monofilament touch sensation threshold testing		x	x	x	x	x	x

*SNAP, sensory nerve action potential; CMAP, compound muscle action potential*.

*^*^Nerve conduction studies will be conducted at 30 month visit when end of study for that subject*.

*Subjects will have either visit 5 (30 months) or visit 6 (36 months) depending on when they enroll. They will not have both. Subjects will be informed at time of enrollment whether they will have a 30 or 36 month visit*.

### Charcot-Marie-Tooth Functional Outcome Measure

The CMT-FOM is a 13-item performance-based physical functioning measure. The items of the CMT-FOM assess upper and lower limb physical functioning, gait, mobility and balance. These items include the nine-hole peg test, functional dexterity test, grip dynamometry, 6-minute walk test (6MWT), 10-meter (10 m) walk/run test, time to climb 4 stairs, 30 second chair stand test, Timed Up and Go test (TUG), dynamometry for ankle dorsiflexion and plantarflexion, and balance items (standing feet apart on a line, eyes open, standing feet apart on a line, eyes closed, standing on one leg, eyes closed) (20, 21). Similar to the CMTPedS (16) and CMTInfS (17), items are scored by converting the raw data to a z-score based on normative data. The z-scores are then categorized as normal = 0, very mild = 1, mild = 2, moderate = 3 or severe = 4, based on the amount of deviation from normal, to generate a total score of 0–52 (21). The CMT-FOM takes ~35 mins to complete. Our initial study of the CMT-FOM demonstrated good test-retest reliability and an association with the CMTES, consisting of the clinical items of the CMTNSv2, providing evidence to support validity (21). As part of this validation study, inter-rater reliability was established following the initial evaluator training at the pre-study investigator meeting (27).

### MRI Assessment for Intramuscular Fat Accumulation

Initial pilot studies examined the utility of MRI to assess changes in muscle and identified fat fraction as a potential biomarker for studies in CMT1A. FF was found to correlate with the CMTES and demonstrated sensitivity to disease progression over a 12-month period (23). To validate this measure for multi-site use in future clinical trials, MRI muscle imaging of the lower extremities will be done using three-point Dixon MRI to assess the %FF of the bilateral thigh and calf muscles. Participants will be imaged feet-first supine with surface matrix coils for lower limb signal reception. Prior to participant enrolment, MRI studies of non-affected individuals will be performed and sent to a central site (UCL) for quality control and analysis (24). MRI scans for participants with CMT1A will also be sent to a central site for analysis.

### *In vivo* Reflectance Confocal Microscopy of Meissner's Corpuscles

*In vivo* RCM of MC has been identified as a novel approach to measure sensory neuropathy (25, 26, 28). MC density of the fingertip of digit V was found to be lower than that of healthy controls and was associated with overall CMT disease severity. In this study, a portable *in vivo* confocal reflectance microscope (Vivascope 3000, Caliber Imaging and Diagnostics Inc.) will be used to assess MC density. *In vivo* RCM of MCs will be performed on the palmar surface of the distal phalanx of digit V and the thenar eminence of the hand. The non-dominant side will be used, unless there is a history of focal trauma, or entrapment neuropathy, that will confound or preclude imaging. In that instance, RCM and touch pressure sensation threshold testing will be done on the dominant side. The *in-vivo* RCM procedure involves applying a few drops of bio-compatible index matching fluid to the skin site, touching the window of the lens to the surface of the skin and obtaining a standardized set of images using the system's operating software (Figure 3).

**Figure 3 F3:**
[figure not shown]
**(A)** On the left, single plane image from *in vivo* reflectance confocal microscopy of digit V. **(B)** In the middle, the MCs are identified by yellow circles in a healthy control. **(C)** On the right, MCs are identified by yellow circles in an individual with CMT 1A.

### Additional Assessments

The CMTNS is a composite measure of disease severity that was developed for use in clinical trials (29). It includes items assessing sensory and motor symptoms, sensation (vibration and pinprick), distal limb strength and limited nerve conduction studies. Following the studies of ascorbic acid in CMT1A, (11, 12) it was modified to improve sensitivity and minimize floor and ceiling effects (CMTNSv2) (14). Most recently, Rasch analysis was applied resulting in the CMTNSv2-R (15). The CMT Exam score (CMTES-R) removes the ulnar motor (CMAP) and radial sensory action potentials (SNAP) amplitudes from the CMTNSv2-R and has been found to be more responsive than the CMTES (30).

Monofilament touch sensation threshold testing will be performed in all participants at the skin sites of *in vivo* RCM of MCs at the hand (digit V and the thenar eminence). Testing will be performed using a 2 Alternative Forced-Choice Stepping Algorithm (31) with a Logarithmic Filament Set. This filament set consists of a series of 9 monofilaments producing magnitudes of force of −3 to 5 in grams in natural log increments at 5/6 of their extended lengths. The nine levels of stimulus forces are available to define 19 threshold levels (32).

The Overall Neuropathy Limitation Scale (ONLS) is a clinician-administered assessment where participants are asked a series of questions about their symptoms and their ability to perform certain tasks and movements. This activity-level measure is designed to distinguish between limitations of upper and lower limbs in individuals with peripheral neuropathies (33).

The CMT Health Index (CMT-HI) is a patient-reported, disease-specific measure of disease burden that was developed for use in clinical trials involving adults with CMT (34). It has been shown to be reliable and valid and has been translated into Italian for multi-site clinical trial use (35).

The Patient Global Impression of Change (PGIC) questionnaire inquires about total health and health related to the symptomatic themes assessed in the CMT-FOM. Participants will be given the option to state that, compared to baseline, their health is: “1—a lot worse”; “2—a little worse”; “3—the same”; “4—a little better”; or “5—a lot better.” The PGIC will be used as an anchor to determine minimal clinically important change for the CMT-FOM.

## Sample Size

We are recruiting 215 individuals with CMT1A to participate in this study. This baseline sample will provide >90% power to detect correlations between the CMT-FOM and existing COAs and PROs as small as 0.22. We anticipate that 180 participants will complete the assessments at the 30-month visit (accounting for up to a 15% dropout). This sample size will provide >80% power to detect significance of a mean change of 0.21 standard deviation units (effect size) using a paired t-test. This effect size was selected as one that is larger than those of existing adult scales such as the CMTNS (0.13) and the CMTES-R (0.20) (36, 37).

A sample of 60 individuals with CMT1A subjects at baseline will provide > 80% power to detect correlations between muscle FF and clinical outcome variables as small as 0.35, using a two-tailed test and a 5% significance level. Anticipating a dropout of 15%, a sample size of 51 CMT1A subjects at 24 months will provide 90% power to detect significance of a mean change of 0.46 standard deviation (SD) units (absolute increase in FF of 0.69%) (23) using a paired t-test. Sample sizes of 51 CMT1A subjects and 21 controls will provide 80% power to detect a group difference in mean change of 0.65%, assuming standard deviations of 1.5% in the CMT1A group and 0.4% in controls (23), using a two-sample t-test. Lastly, for validating RCM of MC density as a sensory biomarker a sample size of 135 CMT1A subjects at baseline will provide >90% power to detect correlations between MC density and clinical outcome variables as small as 0.28. Again, it is anticipated that 115 participants will complete assessments at 30 months which will provide 90% power to detect significance of a mean change of 0.31 standard deviation units using a paired t-test (36).

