## Statistical Considerations

### Validation of the CMT-FOM

Preliminary studies of the CMT-FOM have documented feasibility, content validity, and concurrent validity (21). This study will further validate the CMT-FOM by assessing and documenting inter-rater reliability, performing Rasch analysis, and examining convergent validity and responsiveness. We will also determine the minimal clinically important change. We examined the inter-rater reliability of the CMT-FOM following the investigator meeting and the results have been reported (27). Using baseline data, we will document the internal consistency of the CMT-FOM with Cronbach's alpha.

Given that the CMT-FOM was based on the extensive validation of the CMTPedS (16), we hypothesize that it will be unidimensional and measure the construct of functional ability. We will examine the dimensionality of the CMT-FOM using principal component analysis and confirmatory factor analysis. Misfitting items will be examined and potentially modified, prioritizing integrity of outcome and concept validity. Rasch analysis will be performed on the CMT-FOM, including assessment of the response format, fit of the items, item bias, unidimensionality, and spread of items across the construct being measured (37).

Using data from the baseline visit, correlation and regression analyses will be performed to examine convergent validity. Specifically, we will examine the associations between the CMT-FOM and measures of disease severity (CMTNSv2-R, CMTES-R), patient reported outcomes, such as the CMT-HI, as well as electrophysiological outcomes. We anticipate finding correlations between the CMT-FOM and existing CMT1A measures, but not so strong as to make the CMT-FOM redundant.

To examine sensitivity to change, longitudinal analyses will evaluate the CMT-FOM in all affected subjects evaluated at 0 (baseline), 6, 12, 24, 30 and 36 months. The effect size and standardized response mean (SRM) are the most highly recommended measures of responsiveness (38). These two measures will be computed for CMT-FOM change from baseline, as well as changes in the CMTNSv2-R, CMTES-R, PROs (CMT-HI, PGIC), and the biomarkers at each time point (38, 39). The effect sizes and SRM will be compared between measures using bootstrap resampling (40). Mixed model repeated measures (MMRM) analyses will model mean changes over time in these outcomes (41).

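### The 30-month power figures for CMT-FOM and MC density count nearly every retained participant, although some are assigned a 36-month final visit instead

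*Protocol article*

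**What the plan says.** All statements are in the protocol article.

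- **Sample Size, CMT-FOM.** "We are recruiting 215 individuals with CMT1A to participate in this study". For change over time: "We anticipate that 180 participants will complete the assessments at the 30-month visit (accounting for up to a 15% dropout"; then "This sample size will provide >80% power to detect significance of a mean change of 0.21 standard deviation units (effect size) using a paired t-test".
- **Sample Size, MC density.** The baseline sample is 135. For change over time, "it is anticipated that 115 participants will complete assessments at 30 months", which is said to give "90% power to detect significance of a mean change of 0.31 standard deviation units using a paired t-test".
- **Measures.** Depending on when they enrol, "participants will complete either a 30- or a 36-month end of study visit, but not both". The footnote to Table 1 repeats this: visit 5 (30 months) or visit 6 (36 months), set by enrolment date and made known to the participant at enrolment.
- **Validation of the CMT-FOM.** Sensitivity to change is to be examined in "all affected subjects evaluated at 0 (baseline), 6, 12, 24, 30 and 36 months", with effect size and standardised response mean (SRM) computed at each time point. The paragraph on minimal clinically important change also lists 30 and 36 months separately.

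The article does not say what share of participants is assigned to each final visit. It also does not define a time point that pools the two.

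**The concern.** The counts of 180 and 115 are what remains of the whole cohort after about 15% dropout. The text attributes the whole reduction to dropout and makes no allowance for participants whose final visit is at 36 months. Those participants have no 30-month assessment, so they cannot contribute to a paired comparison of baseline with 30 months.

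Responsiveness to progression is one of the study's stated goals, and these two sentences are the only power basis given for it for CMT-FOM and MC density. The CMT-FOM effect size of 0.21 SD was chosen to lie just above the 0.20 quoted for the CMTES-R, so a modest loss of participants changes what the study can claim to detect. A related consequence is that effect sizes and SRMs reported separately at 30 and 36 months would come from different enrolment cohorts, and a difference between them could not be read simply as six more months of progression.

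**Working it through.** **Inputs.** From Sample Size: 215 and 135 participants at baseline, up to 15% dropout, 180 and 115 completers, effect sizes 0.21 and 0.31 SD, paired t-test. From Measures and the Table 1 footnote: a 30- or a 36-month final visit, never both. Assumption: two-sided 5% level, which the article states for the MRI correlation and which is taken to apply to the paired tests too. The 30/36-month split is not given, so a range is shown.

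**Step 1: origin of the counts.**
- CMT-FOM: 215 × (1 − 0.15) = 182.75, against 180 stated.
- MC density: 135 × (1 − 0.15) = 114.75, against 115 stated.

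At 15% dropout, having 180 at 30 months leaves 2 or 3 participants for the 36-month visit. For MC density, having 115 leaves none.

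**Step 2: reproduce the stated power.** For a paired t-test, power = P(|T| > t₀.₉₇₅,ₙ₋₁), where T is noncentral t with n − 1 degrees of freedom and noncentrality d√n.
- n = 180, d = 0.21: noncentrality 0.21 × √180 = 2.82, power 80.0%.
- n = 115, d = 0.31: noncentrality 0.31 × √115 = 3.32, power 90.9%.

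Both stated figures reproduce, so the power formula was applied correctly. There is almost no slack: n = 179 gives 79.8%, and n = 111 gives 89.9%. The smallest numbers that reach the stated power are 180 (for 80%) and 112 (for 90%).

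**Step 3: apply the either/or rule.** Take a share of the 180 and 115 completers as having the 30-month visit, and recompute with the same formula.

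| Share with 30-month visit | CMT-FOM n | Power at 0.21 SD | MC density n | Power at 0.31 SD |
|---|---|---|---|---|
| 100% (as stated) | 180 | 80.0% | 115 | 90.9% |
| 90% | 162 | 75.7% | 104 | 87.9% |
| 75% | 135 | 67.8% | 86 | 81.1% |
| 50% | 90 | 50.4% | 58 | 64.1% |

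At a 50% share, the change detectable with 80% power for CMT-FOM is 0.30 SD instead of 0.21. The change detectable with 90% power for MC density is 0.43 SD instead of 0.31.

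**Step 4: what is not touched.** Table 1 schedules CMT-FOM and MC density for everyone at 24 months. The anchor-based mean changes and ROC analyses use 12 and 24 months. MRI ends at 24 months, and its power is stated there with n = 51. The baseline correlation power uses baseline counts only.

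**The case against.** The strongest reply is that 30 months is shorthand for the end of the study: anyone seen at 36 months has been followed past 30, so 180 and 115 are the participants with a final paired change, and the stated power holds. This is plausible and may be what was meant. But Sample Size names the 30-month visit, Table 1 makes it a different visit from the 36-month one, and the analysis text lists the two separately. Nothing in the article pools them, so the reading has to be written in.

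A second reply is that the paired t-test appears only as a sample-size device, while the planned analysis of change is a mixed model for repeated measures (MMRM) that keeps the 6-, 12- and 24-month data of those assigned to 36 months. That stands, and it limits the point: the lower figures apply to the 30-month paired test on which power is stated, not to the MMRM.

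Three stronger readings may tempt a reader, and the article does not support them.
- **That 180 and 115 at 30 months are impossible.** The 15% is an upper bound and the split is not given. The counts could occur if dropout and 36-month assignment together removed no more than 35 of 215 (215 − 180) and no more than 20 of 135 (135 − 115).
- **That the MMRM is defective because nobody informs the covariance between 30 and 36 months.** The article does not say whether these are separate visit levels or which covariance structure is used. It is commonly left to the analysis plan.
- **That the list of visits in Validation of the CMT-FOM claims both final visits for every participant.** It can be read simply as the schedule.

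**Conclusion.** The point holds as an inconsistency between the stated power and the visit schedule. The power calculation itself is correct for the counts entered; the counts do not fit the 30-month visit to which they are attached. At the article's own dropout figure, they fail once more than a token number of participants are assigned to 36 months. Even a 10% share at 36 months takes the 30-month test below both stated levels (75.7% against more than 80%; 87.9% against 90%). At an even split the shortfall is large (50.4% and 64.1%).

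These sizes rest on three assumptions: a two-sided 5% level, retention of exactly 180 and 115, and the assumed split. They do not show that the study as a whole is underpowered to detect change.

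**What to change.** Preferred: in Sample Size, define the powered time point as one pooled end-of-study visit (30 or 36 months, whichever the participant is assigned). The counts of 180 and 115 and the stated power then hold. In the analysis text, report effect size and SRM at 24 months, the last visit common to all participants, and at that pooled visit, because separate 30- and 36-month values come from different enrolment cohorts. The planned MMRM need not be replaced.

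Alternative: keep the 30-month test, state the expected 30/36-month split, and restate the power for the number assigned to 30 months.

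Cost: wording and, for the alternative, a short recalculation; no new data or visits. The downside of the first option is that the pooled change mixes 30 and 36 months of follow-up. The downside of the second is that the stated power becomes lower.
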